**Fig 1 pone.0355677.g001:**
[figure not shown]
SPIRIT schedule of enrollment, interventions, and assessments for the PROGAIN trial. The figure displays the planned schedule of participant enrollment, intervention administration, and study assessments at each visit from screening through 12-month follow-up. *If first defecation is not documented before discharge, it will be rechecked at postoperative day 14. APCT, abdominopelvic computed tomography; CAR, C-reactive protein–to-albumin ratio; CRP, C-reactive protein; GLIM, Global Leadership Initiative on Malnutrition; mGPS, modified Glasgow Prognostic Score; NRS-2002, Nutritional Risk Screening 2002; ONS, oral nutritional supplement; PN, parenteral nutrition; PNI, Prognostic Nutritional Index; POD, postoperative day; UUN, urinary urea nitrogen.

### Sample size

The primary outcome is the nitrogen balance on POD 5, expressed in grams per day, compared between the two arms. The sample size calculation is based on a two-sample t-test of independent means. In the absence of a directly comparable randomized trial of high-protein versus conventional PN in patients undergoing gastric cancer surgery, the assumed effect size and variability were derived from related studies of postoperative nitrogen balance under modified protein and amino-acid support [13,14] and from clinical considerations of the smallest between-group difference that would be regarded as clinically meaningful in this population. A between-group mean difference of 3 g/day in postoperative nitrogen balance was assumed, with a common standard deviation of 5 g/day. Using a two-sided significance level of 0.05 and statistical power of 80%, the minimum required sample size is 44 participants per arm (88 participants in total). Anticipating a combined withdrawal, protocol non-completion, or missing primary outcome rate of approximately 20%, the planned enrollment is increased to 55 participants per arm, giving a total target enrollment of 110 participants. The 20% inflation is an allowance for missingness of the POD 5 primary outcome — incomplete 24-hour collection, early events, PN discontinuation, or death before POD 5 — rather than attrition during the 12-month follow-up; it is a conservative estimate consistent with the completeness typically achievable for a fixed-day metabolic endpoint and with attrition reported in comparable post-gastrectomy nutrition trials [26,27]. Because scheduled PN coverage on POD 5 is 50%, the between-arm difference in delivered nitrogen on the primary-endpoint day is approximately 1.0–1.2 g/day, with a cumulative difference of roughly 8 g over the six-day intervention; the assumed 3 g/day balance difference therefore exceeds the single-day intake difference and, if observed, would indicate a genuine difference in nitrogen retention rather than intake alone. The sensitivity of statistical power to the assumed effect size and standard deviation is summarized in S5 Table.

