**Caloric target and dose calculation.** The daily caloric target during the intervention period is set at 20 kcal/kg/day, in keeping with current evidence supporting permissive hypocaloric feeding to avoid perioperative overfeeding. Body weight used for dose calculation is determined by body mass index (BMI): actual body weight is used for participants with BMI < 25 kg/m², and ideal body weight—calculated as height (m)² × 23 (a reference body-mass index of 23 kg/m², consistent with recommendations for Asian populations) [21], applied to both sexes—is used for those with BMI ≥ 25 kg/m². The required daily PN volume is back-calculated from the caloric target using the energy density of the assigned product (0.69 kcal/mL for the control and 0.67 kcal/mL for the investigational product), rounded to the nearest 1 mL, and delivered through a volumetric infusion pump. The calculated daily volume is not expected to exceed the manufacturer-stated maximum of 40 mL/kg/day. For a 75-kg participant, the control formulation delivers approximately 68 g of amino acid per day (0.9 g/kg) and the high-protein formulation approximately 84 g (1.1 g/kg); detailed examples are provided in S2 and S3 Tables. These amino-acid amounts represent PN-only delivery; the total protein supply (oral plus parenteral) that forms the basis of the nitrogen-balance calculation is higher, and the between-arm difference should be interpreted as a difference in PN-delivered rather than total protein.

**Stepwise PN delivery schedule.** PN is administered through a peripheral intravenous line; central venous access is not required. Peripheral access was chosen to avoid the infection and thrombosis risks of central venous catheterisation, consistent with the broader Enhanced Recovery After Surgery (ERAS) principle of minimizing invasive perioperative procedures. PN is initiated on the preoperative day (preoperative day −1; POD −1), withheld on the day of surgery (POD 0) because of perioperative anaesthetic and surgical considerations, and resumed from POD 1 through POD 5, for a total of six administration days. The PN dose on each day is delivered as a fixed proportion of the daily caloric target, decreasing stepwise as anticipated oral intake advances: 80% on POD −1, 100% on POD 1, 60% on POD 2 and POD 3, and 50% on POD 4 and POD 5. The stepwise schedule is summarized in Table 3.

**Table 3 pone.0355677.t003:** Stepwise perioperative parenteral nutrition delivery schedule.

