### Statistical analysis

**Analysis populations.** All efficacy analyses are performed in the intention-to-treat (ITT) population, comprising all randomized participants analyzed in the group to which they were allocated. The per-protocol population is defined as participants who completed the planned PN intervention through POD 5, received at least 90% of the planned cumulative allocated PN volume or amino acid dose, completed the POD 5 nitrogen balance assessment, and had no prespecified major protocol deviations; this population will be used for sensitivity analyses of the primary and key secondary outcomes. The safety population comprises all participants who received at least one administration of allocated PN.

**Primary analysis.** The primary outcome is compared between the investigational and control arms using a two-sample t-test, with the between-group mean difference reported with a 95% confidence interval; the Wilcoxon rank-sum test is used as a sensitivity analysis if distributional assumptions are clearly violated. In a prespecified adjusted analysis, POD 5 nitrogen balance is modelled by analysis of covariance (ANCOVA) with treatment arm as the factor and extent of gastric resection and baseline nutritional status as covariates.

**Mechanistic analyses of the primary endpoint.** To separate the arithmetic and metabolic components of the endpoint, prespecified mechanistic analyses compare between arms (a) total nitrogen intake, (b) urinary urea nitrogen excretion, and (c) net nitrogen retention on POD 5, and evaluate nitrogen-utilization efficiency (net retention relative to delivered nitrogen), and, in an exploratory analysis, adjust the primary endpoint for delivered nitrogen as a covariate. Because delivered nitrogen is a post-randomization variable largely determined by treatment allocation, adjustment for it cannot by itself causally separate nitrogen delivery from nitrogen utilization; these analyses are exploratory and descriptive, use already-recorded variables, and are reported with 95% confidence intervals as hypothesis-generating without causal claims. The partial dependence of nitrogen balance on nitrogen intake is acknowledged as a limitation that these analyses are designed to characterize.

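### An observed 3 g/day difference in nitrogen balance would not by itself show retention beyond intake, because the Sample size section ignores sampling error and uses a PN-only comparator

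*Protocol article*

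**What the plan says.** The Sample size section of the protocol article sets the target effect: "A between-group mean difference of 3 g/day in postoperative nitrogen balance was assumed", "with a common standard deviation of 5 g/day". From these, "the minimum required sample size is 44 participants per arm (88 participants in total"), and after a 20% allowance for a missing POD 5 outcome "the planned enrollment is increased to 55 participants per arm, giving a total target enrollment of 110 participants".

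The same section notes that PN coverage on POD 5 is 50%, so the arms should differ by about 1.0–1.2 g/day in delivered nitrogen that day. Since 3 exceeds that figure, the section concludes that such a difference, "if observed, would indicate a genuine difference in nitrogen retention rather than intake alone".

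Three other places bear on this:

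- Outcomes, Primary outcome: the balance adds oral nitrogen to parenteral nitrogen, then subtracts urinary urea nitrogen (UUN) and a constant of 4 g.
- Interventions, Caloric target and dose calculation: of the worked amino-acid amounts, the protocol says that "the between-arm difference should be interpreted as a difference in PN-delivered rather than total protein".
- Statistical analysis, Mechanistic analyses of the primary endpoint: total nitrogen intake, UUN and net retention are each compared between arms, and these analyses are "reported with 95% confidence intervals as hypothesis-generating without causal claims".

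**The concern.** The sentence states in advance what a result equal to the target effect would mean. Three things about it look wrong.

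1. It compares an observed value with 1.0–1.2 g/day as if the observed value had no sampling error. The trial is powered against a difference of zero, not against the intake difference.
2. The 1.0–1.2 g/day is the scheduled PN difference. The endpoint also contains oral nitrogen, which is self-reported in an open-label trial; the Blinding paragraph itself names this as a possible ascertainment bias. What has to be exceeded is the difference in total intake.
3. It draws a firm conclusion on intake versus retention from a cruder comparison than the mechanistic analyses, which the protocol restricts to hypothesis generation.

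At stake is the step from an improved calculated balance to a claim about protein metabolism. The Introduction says the trial tests for true net retention, so this sentence is likely to be relied on if the trial is positive.

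**Working it through.** **Inputs.** Difference 3 g/day, SD 5 g/day, two-sided α 0.05, power 80%, 44 evaluable and 55 enrolled per arm (Sample size). Nitrogen content 5.21 and 6.17 mg/mL (Table 2). Energy density 0.69 and 0.67 kcal/mL, target 20 kcal/kg/day, 50% coverage on POD 5 (Interventions). Two-sample t-test with 95% CI (Primary analysis).

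**The plan's own figures.**

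- Sample size: n = 2 × (1.960 + 0.842)² × 5² ÷ 3² = 43.6, so 44 per arm, and 44 ÷ 0.80 = 55. Both reproduce. The exact t-test calculation gives 44.6, that is 45, a trivial difference.
- Delivered nitrogen at full dose: control 20 ÷ 0.69 × 5.21 ÷ 1000 = 0.1510 g/kg/day; investigational 20 ÷ 0.67 × 6.17 ÷ 1000 = 0.1842 g/kg/day; difference 0.0332 g/kg/day. At 50% this is 0.99 g at 60 kg and 1.19 g at 72 kg. The stated 1.0–1.2 g/day reproduces.

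**Interval around an observed 3.0.** CI = 3 ± t(0.975, 2n − 2) × 5 × √(2/n), with 1.0–1.2 taken as a known constant.

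| Evaluable per arm | SE | Half-width | 95% CI | Two-sided p against 1.0 to 1.2 |
|---|---|---|---|---|
| 44 | 1.066 | 2.12 | 0.88 to 5.12 | 0.064 to 0.095 |
| 55 | 0.953 | 1.89 | 1.11 to 4.89 | 0.038 to 0.062 |

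At 44 per arm the whole 1.0–1.2 range lies inside the interval. At 55 per arm only 1.11–1.2 does. The lower limit first passes 1.0 at 50 per arm and 1.2 at 61 per arm.

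**How often the data could separate the two.** If the true difference is 3, the 95% CI excludes 1.0 in 46% of trials and 1.2 in 39% at 44 per arm (55% and 46% at 55 per arm). For 80% power, 99 evaluable per arm would be needed against 1.0 and 122 against 1.2.

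**Sensitivity to the SD.** At 44 per arm the lower limit is 1.30 for SD 4, 1.09 for SD 4.5, 0.67 for SD 5.5 and 0.46 for SD 6. At SD 4 the interval would clear 1.2.

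**What beyond intake means in this formula.** The constant 4 cancels between arms, so, with Δ as high-protein minus control:

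Δbalance = Δ(total nitrogen intake) − ΔUUN, hence Δbalance − Δ(total intake) = −ΔUUN.

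A balance difference larger than the intake difference is therefore the same thing as lower UUN in the high-protein arm. With equal oral intake, a balance difference of 3 requires UUN lower by 3 − 1.2 = 1.8 to 3 − 1.0 = 2.0 g/day. The primary test against zero does not examine this.

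**Size of the oral term (hypothetical).** An oral difference of 1.8 g nitrogen, or 1.8 × 6.25 = 11.25 g protein per day, would alone turn 1.2 into 3.0. The protocol gives no estimate of any oral difference between arms; the figure only gives the scale.

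**The case against.** The strongest reply is that this is an explanatory remark and not an analysis. The primary endpoint is the only confirmatory analysis, nothing in the protocol sets a decision criterion at 3 g/day, and the mechanistic section already plans the intake and UUN comparisons with 95% CIs while acknowledging that balance depends partly on intake. That is correct: the sentence is not a formal decision rule, and no planned test or sample size is wrong because of it. But it still says what the target effect would show, and it says so more firmly than the mechanistic section allows.

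A reader might infer that the retention conclusion would be false. The documents do not support that. If the true difference were only 1.0–1.2, an observed 3 or more would occur in 3.0–4.6% of trials at 44 per arm and 1.8–3.0% at 55, so it would be some evidence, given equal oral intake and SD 5. A reader might also infer that the interval always covers all of 1.0–1.2. It does at 44 per arm, but not at 55.

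On oral intake, chance imbalance is already part of the variability of the balance, so it should not be counted twice. What remains is a systematic difference in eating or reporting, which the protocol discloses but which this sentence disregards.

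Finally, equal UUN in the two arms would mean that all the extra nitrogen was kept in the calculated balance, which is retention in one sense. That is a fair reason to report such a result as improved net balance. It is not a difference beyond intake, which is what the sentence claims.

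**Conclusion.** The sentence is wrong as written: the conclusion is unsupported, not disproved. On the plan's own assumptions an observed 3 g/day has a lower 95% limit of 0.88 at 44 evaluable per arm, below the whole PN difference, and 1.11 at 55 per arm, still below 1.2. Independently of sample size, the comparator omits oral nitrogen, and the strength of the claim conflicts with the exploratory status of the mechanistic analyses.

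The figures assume SD 5 and an intake difference known without error. Using 44 per arm assumes the planned 20% missingness and that multiple imputation recovers little information. A smaller SD (4) would remove the overlap with 1.0–1.2, but not the problem with the comparator or the conflict with the mechanistic section. The primary test of balance against zero is unaffected.

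**What to change.** Delete the clause in the Sample size section that says what an observed 3 g/day would indicate. In its place, state that a positive primary result shows improved net nitrogen balance. Then add that a difference beyond intake is suggested, as exploratory evidence in line with the mechanistic section, only if the 95% CI of the between-arm UUN difference (high-protein minus control) lies wholly below 0. Equivalently, the lower limit of the balance difference minus the total nitrogen-intake difference must exceed 0, computed in the same participants or imputed datasets.

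This needs no new data, because both comparisons are already planned. It relies on an assay performed without knowledge of allocation, and reported oral intake cancels out of it.

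The cost is a stricter condition for the metabolic interpretation. The protocol gives no SD for UUN, so the power of that comparison is unknown. It also remains sensitive to incomplete urine collection, which the protocol says is not verified by creatinine.

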### Data collection and management

Trial data are recorded by the enrolling investigator and the CRC on a study-specific case report form. Source documents include the participant’s electronic medical record, laboratory results, abdominopelvic computed tomography images, and the participant-completed meal-by-meal oral intake form; each entry is dated and initialled by the recorder, and entries are reviewed for completeness and consistency by the CRC with discrepancies resolved against source documents. Trial documents identifying participants are stored in locked, access-controlled facilities at the participating institution; participants are identified in trial datasets by a study identifier (PROGAIN-NNN) without direct personal identifiers. Trial records will be retained in accordance with applicable Korean regulations and institutional requirements.

### Statistical analysis

**Analysis populations.** All efficacy analyses are performed in the intention-to-treat (ITT) population, comprising all randomized participants analyzed in the group to which they were allocated. The per-protocol population is defined as participants who completed the planned PN intervention through POD 5, received at least 90% of the planned cumulative allocated PN volume or amino acid dose, completed the POD 5 nitrogen balance assessment, and had no prespecified major protocol deviations; this population will be used for sensitivity analyses of the primary and key secondary outcomes. The safety population comprises all participants who received at least one administration of allocated PN.

**Primary analysis.** The primary outcome is compared between the investigational and control arms using a two-sample t-test, with the between-group mean difference reported with a 95% confidence interval; the Wilcoxon rank-sum test is used as a sensitivity analysis if distributional assumptions are clearly violated. In a prespecified adjusted analysis, POD 5 nitrogen balance is modelled by analysis of covariance (ANCOVA) with treatment arm as the factor and extent of gastric resection and baseline nutritional status as covariates.

**Mechanistic analyses of the primary endpoint.** To separate the arithmetic and metabolic components of the endpoint, prespecified mechanistic analyses compare between arms (a) total nitrogen intake, (b) urinary urea nitrogen excretion, and (c) net nitrogen retention on POD 5, and evaluate nitrogen-utilization efficiency (net retention relative to delivered nitrogen), and, in an exploratory analysis, adjust the primary endpoint for delivered nitrogen as a covariate. Because delivered nitrogen is a post-randomization variable largely determined by treatment allocation, adjustment for it cannot by itself causally separate nitrogen delivery from nitrogen utilization; these analyses are exploratory and descriptive, use already-recorded variables, and are reported with 95% confidence intervals as hypothesis-generating without causal claims. The partial dependence of nitrogen balance on nitrogen intake is acknowledged as a limitation that these analyses are designed to characterize.

**Secondary outcomes, subgroups, and missing data.** The single primary endpoint is the sole confirmatory analysis (two-sided α = 0.05). Two key secondary endpoints — POD 3 nitrogen balance and early change in prealbumin, both objective, blinded, and responsive to short-term protein delivery — are controlled for family-wise error at 0.05 by the Holm procedure, independently of the primary result. All other outcomes are exploratory, reported as point estimates with 95% confidence intervals without multiplicity adjustment and interpreted as hypothesis-generating; postoperative complications are additionally analyzed with multivariable adjustment for extent of resection, surgical approach, and comorbidity, and a subgroup analysis by extent of resection (total versus distal gastrectomy) is prespecified as exploratory via a treatment-by-subgroup interaction. Following ICH E9(R1), the primary estimand is the between-arm difference in mean POD 5 nitrogen balance in the intention-to-treat population under a treatment-policy strategy: PN dose reduction or discontinuation is handled by using the observed POD 5 value and is not treated as missing. Genuine missing data (death before POD 5 or failed collection) are addressed by multiple imputation under missing-at-random as the primary approach, with complete-case analysis as sensitivity; because complication-related missingness may be non-random, a delta-adjusted (tipping-point) sensitivity analysis is performed.

**Other considerations.** No interim efficacy analysis is planned. The full statistical analysis plan, including detailed analysis specifications for each outcome, is finalised and dated before release of the coded treatment labels for the primary analysis. All analyses are conducted using R (R Foundation for Statistical Computing, Vienna, Austria).

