**Methods and analysis:**

PROGAIN is a single-center, randomized, open-label, parallel-group superiority trial with blinded laboratory assessment and coded-group analysis of the primary endpoint. The trial will enroll 110 patients with gastric cancer scheduled for curative gastrectomy. Participants are allocated 1:1 to high-protein PN or conventional PN, administered through a peripheral intravenous line on the day before surgery and postoperative day (POD) 1 through POD 5. PN is delivered at a daily caloric target of 20 kcal/kg/day using a stepwise schedule informed by an institutional retrospective audit of oral intake. The primary outcome is nitrogen balance on POD 5, calculated using a simplified Blackburn equation. Secondary outcomes include nutritional indices, skeletal muscle index, glycemic control, postoperative complications classified by Clavien–Dindo grade and functional recovery measures. The primary analysis will compare the two arms using a two-sample t-test in the intention-to-treat population. The trial has 80% power to detect a between-group mean difference of 3 g/day at a two-sided α of 0.05.

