### Randomization and allocation concealment

**Random sequence generation.** Eligible participants are randomly allocated in a 1:1 ratio. The master allocation sequence was generated in advance for 120 sequential allocations using a custom Python script, with a fixed seed and permuted blocks of variable size (4 and 6) in randomly chosen order. Stratified randomization is not used because the anticipated low proportion of total gastrectomy would produce imbalanced strata and incomplete blocks in the small stratum; extent of gastric resection and baseline nutritional status are instead controlled analytically through a prespecified covariate-adjusted (ANCOVA) analysis, and a subgroup analysis by extent of resection (total versus distal gastrectomy) is prespecified as exploratory in the Statistical analysis section.

**Allocation concealment.** The master sequence is held in read-only form by a single dedicated clinical research coordinator (CRC) in a password-protected directory inaccessible to any other member of the trial team. The CRC has no role in determining participant eligibility, enrolling or consenting participants, administering the assigned interventions, or assessing study outcomes, ensuring that knowledge of the allocation sequence cannot influence enrollment decisions or outcome assessment. File integrity is verified by a SHA-256 cryptographic checksum computed at the time of sequence generation and stored separately, providing an audit trail against post-hoc modification; allocation concealment per se is ensured by the procedural safeguards described in the Allocation procedure section.

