**Primary outcome**			
Nitrogen balance on postoperative day 5	N balance (g/day) = [oral protein (g) ÷ 6.25 + parenteral nitrogen delivered (g)] − (urinary urea nitrogen (g) + 4); parenteral nitrogen is derived from the product-specific nitrogen content (Table 2) and administered volume [23,24]	POD 5	Two-sample t-test (or Wilcoxon rank-sum if non-normal); intention-to-treat as primary analysis

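### The ANCOVA offered in place of stratified randomization is not the primary analysis, so the confirmatory estimate lacks the covariate control that the protocol describes

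*Protocol article*

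**What the plan says.** The section Randomization and allocation concealment gives the reason for not stratifying: "Stratified randomization is not used because the anticipated low proportion of total gastrectomy would produce imbalanced strata and incomplete blocks in the small stratum". It then names the substitute: "extent of gastric resection and baseline nutritional status are instead controlled analytically through a prespecified covariate-adjusted (ANCOVA) analysis". The Trial status section makes the same pairing when it describes amendment 1.2, which changed the text from stratified to non-stratified blocks with prespecified covariate adjustment.

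The analysis sections rank the methods differently:

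- Abstract: "The primary analysis will compare the two arms using a two-sample t-test in the intention-to-treat population".
- Table 4, primary outcome row: "Two-sample t-test (or Wilcoxon rank-sum if non-normal); intention-to-treat as primary analysis".
- Sample size: the calculation is for a two-sample t-test of independent means.
- Statistical analysis, Primary analysis: "The primary outcome is compared between the investigational and control arms using a two-sample t-test". The ANCOVA follows as a separate prespecified adjusted analysis, "with treatment arm as the factor and extent of gastric resection and baseline nutritional status as covariates".

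The single primary endpoint is the sole confirmatory analysis, at two-sided α = 0.05.

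Two further statements bear on the covariates. Under Eligibility criteria, eligibility rests on the planned extent of resection, and a participant whose actual operation differs is retained. Under Caloric target and dose calculation, PN is dosed per kg of a BMI-dependent body weight, while the endpoint is in absolute g/day.

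**The concern.** A reader of the randomization section would expect the comparison that decides the trial to be adjusted for extent of resection and nutritional status, because that adjustment is what the protocol offers in place of stratification. The confirmatory t-test contains neither factor, so the control exists only in an analysis of lower rank.

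Two things are at stake. Any chance imbalance between arms in total versus distal gastrectomy, or in baseline nutritional status, passes unadjusted into the confirmatory estimate. And whatever outcome variance these factors explain stays in the error term, in a trial planned at 80% power with no adjustment counted.

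**Working it through.** **1. The plan's own figure.** Inputs from the Sample size section: difference 3 g/day, SD 5 g/day, two-sided α 0.05, power 80%, 20% loss.

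n per arm = 2 × (1.960 + 0.842)² × 5² ÷ 3² = 43.6, rounded up to 44. Then 44 ÷ 0.80 = 55 per arm, 110 in total. Both stated figures reproduce. The noncentral t distribution gives 79.5% power at 44 per arm and needs 45 for 80%, a trivial difference.

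**2. Power if the ANCOVA were primary.** Residual SD = 5 × √(1 − R²), where R² is the share of outcome variance explained by the covariates. The document gives no R², so the values below are assumptions. Power is noncentral t at 44 per arm, with two degrees of freedom spent on covariates. The equivalent sample increase is 1 ÷ (1 − R²) − 1.

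| Assumed R² | Residual SD (g/day) | Power | 95% CI half-width (g/day) | Equivalent sample increase |
|---|---|---|---|---|
| 0% | 5.00 | 79.4% | 2.12 | 0% |
| 5% | 4.87 | 81.4% | 2.07 | 5% |
| 10% | 4.74 | 83.5% | 2.01 | 11% |
| 20% | 4.47 | 87.5% | 1.90 | 25% |
| 30% | 4.18 | 91.4% | 1.77 | 43% |

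If the covariates explain nothing, adjusting costs about 0.1 percentage point (79.5% to 79.4%).

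**3. Which R² is plausible for resection extent alone.** For a binary factor with prevalence p and outcome shift d, R² = d² × p(1 − p) ÷ 25. Assume p = 10–30% total gastrectomy and d = 1–3 g/day; neither is in the document. The lower end is 1 × 0.09 ÷ 25 = 0.4%, the upper end 9 × 0.21 ÷ 25 = 7.6%. Values of 20–30% would have to come mainly from nutritional status or other covariates.

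**4. Size of a chance imbalance.** The SD of the between-arm difference in the share with total gastrectomy is √(2p(1 − p) ÷ 44), or 6 to 10 percentage points for p = 10–30%. A 1.96-SD imbalance moves the unadjusted difference by 1.96 × 0.064 × 1 = 0.13 g/day at the low end and 1.96 × 0.098 × 3 = 0.57 g/day at the high end: about 0.1–0.6 g/day against a target of 3 g/day.

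**5. Dosing weight.** Table 2 gives 0.151 and 0.185 g nitrogen/kg/day at full target. At the 50% coverage scheduled for POD 5, each kg of dosing weight carries 0.076 to 0.093 g/day of delivered nitrogen. With an assumed weight SD of 10 kg, that is an SD of 0.76–0.93 g/day, or roughly 2–3% of a variance of 25. This covers the delivery route only; the documents do not show how weight relates to oral intake or urinary loss.

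**6. Validity.** In a simulation of 8,000 trials per setting (44 per arm, assumed 20% total gastrectomy, R² of 0, 10 and 30%), type I error was 4.8–5.2% for the t-test and 4.7–5.1% for the ANCOVA.

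**The case against.** The case for leaving the plan alone has weight. The randomization section never says that the ANCOVA is the primary test; it promises a prespecified ANCOVA, and the Statistical analysis section supplies one with exactly those two covariates. The t-test is named consistently as primary and the sample size is built on it. An adjusted estimate will be reported in any case. The gain depends on an unstated R² and may be only about two points of power. Changing the declared primary analysis during an open-label trial is more than a wording change, particularly when the Trial status section reports three confirmed POD 5 results by the registration date.

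Most of this limits the point without removing it. It still stands that the randomization text presents as control something that the confirmatory estimate does not carry.

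Some stronger readings are tempting and are not supported:

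- A reader might infer that the t-test is biased or inflates type I error. Under unstratified 1:1 randomization it does neither.
- A reader might infer that the trial is undersized. The stated numbers reproduce without any adjustment.
- A reader might infer that stratification was given up because of the ANCOVA. The stated reason is the small total-gastrectomy stratum; the ANCOVA is the substitute.
- A reader might treat the unspecified extent (planned or actual) or the absence of dosing weight as errors. The SAP, which is not available here, may define the covariates, and no text promises adjustment for weight.

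**Conclusion.** The point holds as a mismatch of rank: the covariate control offered in place of stratification sits outside the confirmatory analysis. The cost is some precision and some protection against chance imbalance. Under the assumed R² of 5–30%, the power forgone is about 2 to 12 percentage points; at R² = 0 nothing is forgone. For resection extent alone the lower end is the more plausible, and a fairly extreme imbalance in it would shift the estimate by about 0.1–0.6 g/day under the assumed prevalence and effect. All power figures take the plan's 3 g/day, SD 5 g/day and 44 evaluable per arm as given.

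This is a worthwhile improvement with almost no statistical downside. It does not call the validity of the planned test or the enrollment target into question.

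**What to change.** By a dated protocol and SAP amendment, before the coded labels are released:

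1. Make the ANCOVA of POD 5 nitrogen balance the primary analysis, and report the adjusted mean difference with its 95% CI. Align the Abstract, the primary outcome row of Table 4 and the Statistical analysis section.
2. Define the covariates as arm, planned extent of resection as known before randomization (total or distal), and one named baseline nutritional measure, since the article lists several candidates. Preferably add dosing weight, which is fixed at baseline and needed for every participant's dose.
3. Keep the unadjusted t-test as a supportive analysis.
4. Record in the amendment that no between-group result had been seen when the change was made.

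If the sponsor prefers to keep the t-test as primary, the randomization section should at least say that the two factors are adjusted for only in an additional analysis.

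The cost is the amendment itself, with IRB approval and notice to the registry, which the article already requires for substantial amendments. The sample size of 110 and the data collection stay as they are.
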